#### Concomitant treatment

2.9.5

Other interventions such as medications, injections, physical therapy, surgical procedures, acupuncture, cupping, and moxibustion will not be permitted during the 12-week treatment period (not applicable to the follow-up phase). However, any concomitant medications are taken by the subject within 4 weeks before trial participation, which will not affect the interpretation of the trial outcomes, will be allowed at the discretion of the investigator.

#### fMRI examination procedure

2.9.6

The fMRI examination (PRISMA 3.0T Magnetic Resonance Imaging Scan; Siemens Shanghai Medical Equipment Ltd.) will be performed to collect brain images offering more visualized proof. During the scanning procedure, subjects will be asked to keep quiet and their eyes closed. In the meantime, they need to keep their mind empty but avoid sleeping. The researcher will check whether the participants are awake during the process. The MRI protocol for this study consists of the following parameters: T1 scanning: repetition time (TR) = 2300 ms, echo time (TE) = 2.32 ms, flip angle = 8°, the field of view (FOV) = 240 × 240 mm^2^, matrix size = 256 × 256 mm^2^, voxel size = 0.9 × 0.9 × 0.9 mm^3^, 192 sections, 0.9 mm thickness, 0.45 mm slice gap, 200 Hz/pixel bandwidth. MRS scanning: TR = 1700 ms, TE = 135 ms, 1 mm thickness, no slice gap. DTI scanning: matrix size = 128 mm × 128 mm, FOV = 220 mm × 220 mm, 3.8 mm slice thickness, 33 slices centered on the corpus callosum, b-value = 1000 s/mm^2^. Blood oxygen level dependent scanning: TR = 3000 ms, TE = 30.0 ms, flip angle = 90°, the FOV = 192 × 192 mm^2^, voxel size = 3 × 3 × 3 mm^3^, 36 sections, 3.0 mm thickness.

#### Bone density test

2.9.7

The bone density test (DPX Bravo Dual-energy X-rays Absorptiometry; General Electric Co., Ltd.) will be performed to collect bone mineral density (BMD) data.

### Outcome measure: primary outcomes

2.10

Outcomes will be evaluated using multiple indexes. The primary outcomes are measured by the following therapeutic indexes: Short-Form of McGill Pain Questionnaire (SF-MPQ), Osteoporosis Symptom Score during the observation period (3 months) and follow-up period (1 month). After baseline time, they will be tested at week 0, week 4, week 8 and week 12, and during the follow-up period.

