#### Study schedule

2.9.1

The study schedule is presented in Table 1. At the screening visit, participants will sign the informed consent form. In a baseline questionnaire, the following information will be obtained: age, occupation (physical/nonphysical), education level, last menstrual period, previous use of acupuncture, and expectation to acupoint thread embedding treatment. Moreover, Short-Form of McGill Pain Questionnaire (SF-MPQ), Osteoporosis Symptom Score, Osteoporosis Quality of Life Scale (OQOLS), 16-item Assessment of Health-Related Quality of Life in Osteoporosis (ECOS-16) must be completed at the baseline (week 0). Thereafter, study subjects will be randomized. There is a 3-month study period and a 1-month follow-up period for each group. In the study period, SF-MPQ, OQOLS, ECOS-16, and Osteoporosis Symptom Score will be evaluated every 4 weeks. fMRI and bone density test will be tested 2 times: in week 0 and week 12.

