### Statistical analysis

2.14

Image data processing includes using methods such as independent component analysis (ICA) and function binding, applying professional software such as MRIcro for windows, Xjview 8.1, SPM 12, and Matlab 5.1.

Statistical analysis technique is used to apply a statistical test to the difference of prior-treatment and posttreatment, and to examine the curative effect difference within groups and among groups of all curative effect indexes. We will adopt the 2-sided test for all statistical tests. It is considered that the tested differences are statistically significant if *P* value is less than or equal to .05. If *P* value is greater than or equal to .05, the tested differences are not statistically significant. Details are as following.

Measurement data includes the *t* test will be adopted to run comparison among groups. When it does not comply with the normal distribution, we will choose Wilcoxon rank-sum test. Similarly, we will run paired *t* test toward the difference of prior-treatment and post-treatment, and it will be changed into Wilcoxon rank-sum test, while it does not comply with the normal distribution.

Enumeration data: We will use the Chi-square test, calibration Chi-square test, and Fisher exact method to run comparison among groups.

Ranked data: Wilcoxon rank-sum test will be applied to run comparison among groups and signed rank-sum test to run comparison within groups.

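### Two unranked primary scales with no primary time, each tested at .05, let the chance of a false-positive primary result exceed 5%, and one of the times falls where other treatment is allowed

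*Protocol article*

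**What the plan says.** Section 2.10 (primary outcomes) names two scales: "Short-Form of McGill Pain Questionnaire (SF-MPQ), Osteoporosis Symptom Score during the observation period (3 months) and follow-up period (1 month"). On timing it adds: "After baseline time, they will be tested at week 0, week 4, week 8 and week 12, and during the follow-up period". Section 2.9.1 (Study schedule) says the scales "must be completed at the baseline (week 0"), so week 0 is the baseline itself. It also says that, in the study period, "SF-MPQ, OQOLS, ECOS-16, and Osteoporosis Symptom Score will be evaluated every 4 weeks". That leaves weeks 4, 8, 12 and follow-up as post-baseline times. Neither section 2.10 nor the abstract ranks the scales or picks a visit.

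Section 2.14 (Statistical analysis) compares the arms on all efficacy indexes with t tests or Wilcoxon tests. It states: "We will adopt the 2-sided test for all statistical tests". A difference is significant if the P "value is less than or equal to .05". The next sentence says that if the P "value is greater than or equal to .05, the tested differences are not statistically significant".

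Section 2.9.5 (Concomitant treatment) says other interventions, including medications, physical therapy and acupuncture, "will not be permitted during the 12-week treatment period (not applicable to the follow-up phase").

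**The concern.** A 5% test protects against a false claim only if the comparison that carries the claim is fixed in advance. Here the scale and the visit are both left open within the primary definition. No model that pools the visits is named, and no rule says what combination of results counts as success. A report could therefore put forward whichever scale and visit reached .05 and still call it a primary result.

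Two smaller faults sit in the same rules. The follow-up value is primary, yet participants may then take other treatments. They know their allocation (section 2.8), so the arms may differ in what they take. That value then measures the assigned treatment plus whatever follows it. Also, a P value of exactly .05 falls under both halves of the significance rule.

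**Working it through.** **Plan's own figure.** The only error-rate figure is .05 per test. The protocol gives 35 per arm but no effect size, SD or power for it, so there is no stated power or family-wise error to reproduce.

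**Inputs.**
- Primary scales: 2 (section 2.10).
- Post-baseline times: 4, taking follow-up as one assessment. Table 1 is not readable in the text used, so this is an assumption.
- Level: .05, two-sided (section 2.14).
- Patients per arm: 35 (section 2.2).
- Correlations: not in the protocol. Assumed 0.3–0.9 between visits and 0–0.8 between scales.

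**Count of tests.** 2 × 4 = 8 between-group tests at most. Within-group tests are also planned and are not counted here.

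**Chance of at least one false positive when there is no true difference.** For k independent tests this is 1 − 0.95^k. For correlated tests I used multivariate normal simulation (200,000 draws), with exchangeable correlation over visits multiplied by exchangeable correlation over scales.

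| Reading of the primary outcome | Tests | Independent | Correlated, over the assumed range |
|---|---|---|---|
| Two scales, one time | 2 | 1 − 0.95² = 9.8% | about 8–10% |
| Two scales, weeks 4, 8, 12 | 6 | 1 − 0.95⁶ = 26.5% | about 13–25% |
| Two scales, weeks 4, 8, 12 and follow-up | 8 | 1 − 0.95⁸ = 33.7% | about 14–32% |

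The low end of the eight-test range is at 0.9 between visits and 0.8 between scales (14.3%). The high end is at 0.3 and 0 (31.7%). A middle case of 0.7 and 0.5 gives 22.7%.

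**Price of controlling the error over two scales at one time.** The detectable standardised difference at 80% power is approximately (z for 1 − α/2 + z for 0.80) × √(2/35), where √(2/35) = 0.239.
- α = .05: (1.960 + 0.842) × 0.239 = 0.67; by the t distribution, 0.68.
- α = .025: (2.241 + 0.842) × 0.239 = 0.74; by the t distribution, 0.75.

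**Follow-up.** Section 2.10 keeps the follow-up month inside the primary outcome. Section 2.9.5 ends the ban on other interventions before it. Section 2.6, item 7, makes unapproved use of treatments that can affect the results a ground for withdrawal, with no stated end at week 12. The three sections do not give one consistent account of follow-up.

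**Threshold.** Significant if P ≤ .05 and not significant if P ≥ .05 overlap at P = .05.

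**The case against.** The strongest reply is that eight tests are nowhere stated. In section 2.10 the word for testing most naturally means measuring, since it includes week 0, and section 2.14 speaks of differences before and after treatment without naming a visit. This stands: eight is the most the text permits, and a reader should not take it as the plan. Nor should a reader take the 33.7% as the error rate, because it needs independence, which is implausible for repeated scores in the same women. No sentence says that a single significant result would be enough for a claim either. Even so, the narrowest reading leaves two scales and about 8–10%.

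The trial calls itself exploratory, and a multiplicity method may be set in an analysis plan that is not shown. Both points soften the concern. But the Discussion gives the purpose as verifying efficacy and safety, and it is this document that fixes which outcomes and times are primary.

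A reader might infer that the follow-up comparison is invalid or confounded. That goes too far: comparing randomised arms regardless of later treatment is legitimate, but it answers a different question from the week-12 comparison. The withdrawal criterion may also limit such use.

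A reader might also take the .05 rule for all tests to mean uncorrected voxel-wise imaging tests. The protocol does not support this. Image processing has its own paragraph, the rule follows in a paragraph about efficacy indexes, and section 2.12 directs the imaging at the hypothalamus, the limbic system and circuit connections.

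**Conclusion.** The concern holds in a limited form. The primary outcome is fixed as two unranked scales over several times with no primary time, and .05 is applied to each test. Followed as written, the chance of a false-positive primary result is above 5%: about 8–10% if only one time is used, and about 14–32% if all four are. These ranges rest on the assumed correlations and on a single follow-up assessment. The exploratory label reduces the weight of the point but does not remove it, given the stated aim to verify efficacy. The follow-up value mixes assigned and later treatment, so sections 2.9.5 and 2.10 need to be reconciled. The overlap at P = .05 is a true contradiction but an editorial one, and matters only for a P value at that boundary. The plan should be changed on these points; none of them makes the trial unusable.

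**What to change.** 1. Make the between-group comparison at week 12 the primary one.
2. Control the error over the two scales, either by Holm or by a fixed sequence. Nothing in the protocol ranks one scale above the other, so the order is the sponsor's to set before analysis.
3. Make weeks 4 and 8 and follow-up secondary. Record other treatments received in follow-up, and reconcile sections 2.9.5 and 2.10 (with section 2.6, item 7) on that phase.
4. State the threshold once: significant if P < .05 (after any adjustment), otherwise not.

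The outcome data needed are already in the schedule. The change does need a protocol amendment and a registry update, since the trial was registered in May 2017 and recruitment began in September 2018. Under Holm the smaller P value must reach .025, so the detectable difference with 35 per arm at 80% power rises from 0.68 to 0.75 SD. Under a fixed sequence the first scale loses no power, but the second cannot be claimed if the first fails.

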### Outcome measure: secondary outcomes

2.11

Outcomes will be evaluated using multiple indexes. The secondary outcomes are measured by the following therapeutic indexes: Osteoporosis Quality of Life Scale (OQOLS), 16-item Assessment of Health-Related Quality of Life in Osteoporosis (ECOS-16). All the outcomes will be evaluated before and after treatment. The safety of interventions will be assessed at every visit. After baseline time, they will be tested at week 0, week 4, week 8 and week 12, and during the follow-up period.

### fMRI and BMD

2.12

fMRI will focus on the activity of the hypothalamus, limbic system, and the connection among neuron circuits to reflect the changes of the brain's function of PMOP patients before and after treatment. BMD will test the density to certain the severity of osteoporosis. fMRI scans and bone density test will be done before and after the observation period to show cranial neuroimaging changes.

### Safety assessment

2.13

At every visit, the physical examination will be performed, and adverse events will be checked. Blood samples will be collected at week 0 and week 12. Blood routine test, liver function (alanine aminotransferase), and kidney function (serum creatinine) will be done at the beginning and the end of the intervention period.

Possible adverse events due to acupoint thread embedding include allergy, local infections, subcutaneous hematoma, and so forth. Any adverse events or reactions that occur during the study process will be addressed properly and analyzed by the investigator. Serious adverse events associated with the trial should be reported to the principal investigator immediately. All unexpected and unintended responses will be documented as adverse events by the researcher at every visit, even if they are not necessarily related to the acupuncture intervention. The details of adverse events will be carefully recorded in the CRF by the corresponding research staff.

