#### Adverse events

2.9.4

During the research, some adverse reactions may occur. Researchers will monitor every patient with adverse reaction.

The following adverse reactions may happen after the acupoint thread embedding:

(1)Local reaction: mostly some sterile inflammation with inflamed hot pain within 5 days. Some cases may be more severe, like a small amount of milky-white exudation at the embedding spot caused by fat liquefaction because of thread stimulation. Circumstances above should not require any special treatment.(2)General reaction: some patients may experience temperature rising after the treatment 4 to 24 hours, which mostly around 38°C. It will fade away in 2 to 4 days by itself. Usually, hemogram of each patient may rise in different levels, and it will return to normal in 3 to 5 days.

If adverse reactions occur, the following treatment will be used.

(1)Pain at implantation acupoint: Apply hot compress.(2)Local swelling, progressive pain, and fever 3 to 4 days after the implantation: Lack of strict asepsis and inappropriate protection of the wound could cause secondary infection, which mostly occurs some inflammatory symptoms. Apply hot compress and anti-infective treatment would help.(3)Nerve injury: It is usually caused by incorrect operation or excessive stimulation or carelessness, and can be avoided with the careful operation.(4)Hemorrhage: It is usually caused by the puncture on the vessels or excessive stimulation, in which case pressure dressing on the puncture point would stop the bleeding.(5)Thread allergy: local itching or swelling or fever can be remitted by antianaphylaxis treatment.

Climen, which includes estradiol and cyproterone acetate, is one of the estrogen and progestogen/anti-androgen (HRT). It is used in HRT for women with an intact uterus, used to substitute for a lack of estrogen production by the ovaries during menopause. It helps prevent postmenopausal bone loss (osteoporosis) and reduce risk of fracture. The most commonly reported side effects when taking Climen include breast tenderness, breast pain, abdominal pain, nausea, edema, headache, depression, changes in body weight, and changes in libido.

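### The adverse event recording sentence in section 2.13 does not literally reach the foreseen reactions listed in section 2.9.4, and conflicts with the text around it

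*Protocol article*

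**What the plan says.** Section 2.13 (Safety assessment) of the protocol article contains four relevant statements:

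- Surveillance: "At every visit, the physical examination will be performed, and adverse events will be checked".
- Examples: "Possible adverse events due to acupoint thread embedding include allergy, local infections, subcutaneous hematoma, and so forth". No Climen effect is named here.
- Analysis: "Any adverse events or reactions that occur during the study process will be addressed properly and analyzed by the investigator".
- Recording: "All unexpected and unintended responses will be documented as adverse events by the researcher at every visit", continuing "even if they are not necessarily related to the acupuncture intervention". The next sentence sends the details of adverse events to the CRF.

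Section 2.9.4 (Adverse events) lists what is foreseen in each arm. For embedding it begins "Local reaction: mostly some sterile inflammation with inflamed hot pain within 5 days". It adds exudation in some cases, a temperature rise to around 38°C, and a raised blood count. For Climen it says "The most commonly reported side effects when taking Climen include breast tenderness, breast pain, abdominal pain, nausea, edema, headache, depression", and the list goes on to changes in weight and libido, nine effects in all. The section also says that patients with an adverse reaction will be monitored.

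**The concern.** The recording sentence is the only one that says which responses become adverse events, and it qualifies them as both unexpected and unintended. The reactions in section 2.9.4 are, by the protocol's own account, expected. Two trained members of staff could therefore both follow the article and record different things: one enters a sore implantation site or breast tenderness, and the other leaves it out because it was foreseen.

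Safety is a stated objective (section 2.1), and the Discussion says that the trial will verify it. The foreseen reactions are likely to be the most frequent harms in each arm, so they are the ones that a safety summary most needs. Several are also short-lived. Section 2.9.4 gives up to 5 days for local pain, 2 to 4 days for fever and 3 to 5 days for the blood count, while sessions are two weeks apart (section 2.9.2) and bloods are taken only at weeks 0 and 12 (section 2.13). Many such reactions could be over before the next session, so whether they reach the CRF depends on staff asking about them and regarding them as recordable.

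**Working it through.** The article states no adverse event rate, so there is no figure to reproduce. The check is mainly a comparison of the texts.

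**Step 1. What the recording sentence covers.** It sets two conditions, unexpected and unintended. Its closing clause removes any condition on relatedness but leaves expectedness in place. It does not contain the word *only*.

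**Step 2. What the neighbouring sentences cover.** The analysis sentence has no limit on expectedness. The examples sentence treats foreseen embedding reactions as adverse events. The CRF sentence has no limit either, but it applies to adverse events and so depends on what has been classed as one. The surveillance and monitoring sentences concern checking and follow-up, not what is entered.

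**Step 3. Set against section 2.9.4.**

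| Foreseen reaction (2.9.4) | Within the recording sentence, read literally? | Named as an example in 2.13? |
|---|---|---|
| Embedding: allergy, local infection | No | Yes |
| Embedding: bleeding | No | In part, as haematoma |
| Embedding: sterile inflammation, exudation, temperature rise, raised blood count | No | No, though the list is open-ended |
| Climen: nine listed side effects | No | No |

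The texts conflict for every row. For the last two rows, no example in section 2.13 resolves the conflict.

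**Step 4. Would the narrow reading bias the comparison in a known direction?** This needs rates that the article does not give, so those below are assumptions for illustration only. Let u be the risk of an unexpected event (taken as equal in both arms) and e the risk of a foreseen reaction, independent of each other. With 35 patients per arm (section 2.2):

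- Full recording: p = 1 − (1 − u)(1 − e), and patients with an event = 35p.
- Narrow recording: 35u.

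For u = 5%, narrow recording gives 35 × 0.05 = 1.75 patients in each arm and a difference of 0. Full recording gives:

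| e, embedding / Climen | p, embedding / Climen | Patients | Difference |
|---|---|---|---|
| 30% / 30% | 0.335 / 0.335 | 11.7 / 11.7 | 0 |
| 50% / 30% | 0.525 / 0.335 | 18.4 / 11.7 | +19 points |
| 30% / 50% | 0.335 / 0.525 | 11.7 / 18.4 | −19 points |

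For u = 10%, narrow recording gives 3.5 patients per arm. Full recording with e = 50% / 30% gives 0.55 − 0.37 = +18 points, and swapping the arms gives −18 points.

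Under these assumptions narrow recording always lowers the counts. The difference between arms may be unaffected, or a difference in either direction may be hidden. Nothing in the article selects among these cases.

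**The case against.** The strongest reply is that the sentence is inclusive. It says that certain responses will be recorded and does not say that others will not. Its closing clause widens capture, the same paragraph calls foreseen reactions adverse events, and any event or reaction is to be analysed. On a sympathetic reading the authors meant to record everything. Further, a journal article condenses the protocol, and the CRF may already carry a reaction list with fields for relatedness and expectedness.

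Much of this stands. A reader might infer that the protocol *defines* adverse events so as to exclude foreseen reactions; no sentence says so. A reader might also take "Circumstances above should not require any special treatment" as licence not to record, but that sentence concerns treatment of a reaction, not its documentation. Nor can it be claimed that the CRF lacks the relevant fields.

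A reader might infer too that unblinded staff will judge what is unexpected. That is not shown. Section 2.8 blinds the assessor and the data collector, and section 2.13 assigns recording to a researcher and research staff whose blinding status it does not state.

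The reply does not remove the conflict. The sentence is not an omission due to condensing: it is printed, and it carries a qualifier that fits neither section 2.9.4 nor the rest of its own paragraph. Reactions can be analysed reliably only if they are documented.

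**Conclusion.** The point holds as an inconsistency in the recording rule. Sections 2.9.4 and 2.13 do not agree on whether the most common foreseen harms are documented as adverse events. If the recording sentence is applied literally, counts may be too low in either arm.

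It is tempting to go further and say that the safety comparison is understated, or could be reversed. The documents do not support that. They give no reaction rate for either arm and no indication of how staff apply the sentence, so the effect on the comparison has no known direction or size. For the same reasons no number of lost events can be given. The conclusion rests on the wording alone. It is worth correcting because a stated objective depends on this rule and the correction is cheap.

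**What to change.** Reword the recording sentence in section 2.13 to say, in substance, that every untoward occurrence after randomisation, whether or not expected and whether or not related to treatment, is documented as an adverse event in both arms. Record expectedness and relatedness as attributes of each event, not as conditions for entering it; if the CRF already has these fields, only the sentence needs to change. Ask participants in both arms about the same list, made up of the section 2.9.4 reactions for both treatments.

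The cost is one sentence, at most two CRF fields and one common checklist. There will be more non-serious entries, and reported event counts will be higher. Because questions about implantation sites reveal allocation, they should not be put by the blinded outcome assessor. Recruitment had already begun (section 3.1), so the date of the change should be noted, and sites should be asked whether foreseen reactions were being entered before it.
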